### Statistical analysis

5.12

Statistical analysis will be performed using SPSS software version 20.0. The primary analysis will follow the ITT principle, including all randomized participants in their assigned groups regardless of protocol adherence. A secondary PP analysis will include only those participants who complete the assigned intervention without major protocol violations, to assess the robustness of the ITT findings.

Primary and secondary outcomes will be analysed as follows: Continuous data that are normally distributed will be presented as mean ± standard deviation (x ± s), while non‐normally distributed data will be expressed as median (with interquartile ranges). For comparisons of normally distributed continuous data between groups, the independent samples t‐test will be used. The Mann–Whitney U test will be applied for comparisons of non‐normally distributed continuous data. Categorical data will be presented as frequency (rate) and analysed using the chi‐square test or Fisher's exact test. If multivariate analysis is required, multiple linear regression or logistic regression models will be employed, depending on whether the dependent variables are continuous or categorical. Statistical results will be reported as estimates with 95% confidence intervals (CIs), which will be compared to the pre‐specified non‐inferiority margin. Blinded statistical analyses will be performed, with the analyst unaware of group assignments. The group allocation code will remain concealed until the analyses and interpretation have been completed. A predefined subgroup analysis will stratify patients by IP angle (e.g. <30° vs. ≥30°) to evaluate whether anatomical variation influences comparative efficacy and safety. A mixed‐effects model or generalized estimating equations may be employed post hoc to adjust for potential clustering by study centre and assess the robustness of primary findings across sites.

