### Secondary outcomes

3.2

**Final SFR**: SFR at 1 month based on low‐dose CT scan. No residual stone, or no stone fragments larger than 2 mm under CT scan are defined as stone‐free.
**Operative time**: For the FANS f‐URS group, the operative time is characterized as the duration from the insertion of the endoscope into the urethra to the completion of stent placement. For the mini‐PCNL group, the operation time is defined as from retrograde placement of the ureteric catheter to the placement of nephrostomy tubing or removal of percutaneous access.
*
**Postoperative pain levels:** assessed within 24 hours using a 10‐point visual analogue scale (VAS)*.^9^

**Duration of hospital stay**: *Calculated from day of surgery to day of discharge, rounded up to the nearest whole day*.
**Complications:** All adverse events occurring within 1 month post‐procedure, graded by the Clavien–Dindo classification.^10^

**Improvement of Quality‐of‐Life Score**: *Measured preoperatively and at 1 month using the Wisconsin Stone Quality of Life questionnaire*.^14^, ^16^

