### Follow‐up and data collection

5.8

A low‐dose, non‐contrast CT scan with 2‐mm slices will be obtained within 72 hours post‐procedure to assess immediate stone‐free status, defined as no visible stones or only fragments ≤ 2 mm in the bone window. Routine blood tests and serum procalcitonin will be drawn within two hours of surgery to screen for infection, and haemoglobin will be compared between preoperative and two hours postoperative samples; any patient with a haemoglobin below 70 g/l will receive a blood transfusion.

In the FANS f‐URS group, patients with no significant discomfort may be discharged within 24 hours of surgery. In the mini‐PCNL group, if a nephrostomy tube was placed, it will be removed 1–3 days after the effluent becomes grossly clear, followed by patient discharge. All patients will have their 6 Fr double‐J stents removed at two weeks. Health‐related quality of life will be measured using the standardized Wisconsin Stone QoL questionnaire before surgery and again at one month.^14^ Stone composition will be analysed by infrared spectroscopy using a uniform methodology at each centre. At one month, a follow‐up low‐dose non‐contrast CT will be performed only in patients with residual fragments on the 72‐hour scan; those rendered stone‐free at 72 hours will not undergo further imaging.

Patients' characteristics and clinical outcomes will be recorded on a pre‐established case report form (CRFs). Stone size will be defined as the largest diameter of the stone. For multiple stones, the stone size will be defined as the cumulative sum of the maximal diameters of all stones. Grading of hydronephrosis will be evaluated according to the Onen hydronephrosis grading system.^15^ For the FANS f‐URS group, the operative time is characterized as the duration from the insertion of the endoscope per urethral to the completion of stent placement. For the mini‐PCNL group, the operation time is defined as from retrograde placement of ureteric catheter to the placement of nephrostomy tubing or removal of percutaneous access. Hospital stay will be rounded up to the nearest whole day and calculated from the day of surgery to the day of discharge.

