### Sample size

5.11

Based on published literature, the immediate SFR for mini‐PCNL in 1–2 cm lower pole stones is approximately 85%; we therefore assume an immediate SFR of 85% for both the mini‐PCNL and FANS f‐URS arms^8^, ^17^, ^18^. A non‐inferiority margin of 8.5% has been selected, as an absolute reduction in SFR of up to 8.5% is deemed the maximum clinically acceptable loss of efficacy given the benefits of FANS f‐URS (less invasiveness, faster recovery and lower bleeding risk) and aligns with margins used in similar endourological trials.^8^ Using simulations conducted in Stata with an 80% power and an alpha level of 2.5%, the required sample size is 278 participants per group (totalling 556). To account for an anticipated 15% loss to follow‐up or withdrawal, we inflate each arm to 320 participants, yielding a final enrolment target of 640 patients.

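### Quality-of-life improvement is compared without using the baseline score as a covariate; adjusting for it would be more precise and needs no new data

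*Protocol article*

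**What the plan says.** Section 3.2 of the protocol article lists improvement in quality of life as a secondary outcome: "Measured preoperatively and at 1 month using the Wisconsin Stone Quality of Life questionnaire". Section 5.8 repeats that patients complete the "questionnaire before surgery and again at one month". Table 1 places the baseline questionnaire in the screening period, and section 5.4 has baseline assessments finished before randomization. The baseline score is therefore a proper pre-randomization covariate.

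Section 5.12 introduces its list of tests with "Primary and secondary outcomes will be analysed as follows". For continuous data it then states: "For comparisons of normally distributed continuous data between groups, the independent samples t‐test will be used". Otherwise the Mann–Whitney "U test will be applied for comparisons of non‐normally distributed continuous data". No baseline covariate is mentioned. The nearest thing to an adjusted analysis is "If multivariate analysis is required, multiple linear regression or logistic regression models will be employed", which gives no trigger, covariate or endpoint. The mixed-effects or GEE option in the same section is described as post hoc and deals with clustering by centre.

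**The concern.** Comparing improvements by a two-sample test amounts to subtracting the whole baseline score from the 1-month score. That is the most efficient use of the baseline only if the regression slope of the 1-month score on baseline equals 1. When the slope is lower, the subtraction adds baseline noise to the estimate. ANCOVA estimates the slope from the data and removes only the part of the variation that baseline predicts.

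The endpoint is not incidental. Section 2 makes health-related quality of life a secondary objective. The Discussion says that non-inferiority together with clear advantages in safety, recovery or patient-reported outcomes could guide recommendations towards FANS f-URS. Precision on the trial's only multi-item patient-reported instrument is worth keeping, and the data needed are already being collected.

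**Working it through.** **The plan's own figure.** The article states no standard deviation, correlation or power for quality of life. Its only sample-size figure is for the primary outcome: "80% power and an alpha level of 2.5%, the required sample size is 278 participants per group". The inputs are an 85% stone-free rate in both arms ("we therefore assume an immediate SFR of 85% for both the mini‐PCNL and FANS f‐URS arms"), a margin of 8.5 percentage points and one-sided 2.5%:

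n = (1.960 + 0.842)² × 2 × 0.85 × 0.15 / 0.085² = 277.0, rounded up to 278 per arm (power 80.1%).

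The figure reproduces. It is used below only as a convenient number of evaluable patients per arm.

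**Variances.** Let s0 and s1 be the standard deviations of the score at baseline and at 1 month, and r their correlation. For a given number of patients, the variance of the estimated treatment effect is proportional to:

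- change score: s0² + s1² − 2·r·s0·s1
- 1-month score alone: s1²
- ANCOVA: s1²(1 − r²)

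Change score minus ANCOVA is (s0 − r·s1)², which is never negative. It is zero only when r × s1/s0 = 1. The 1-month score minus ANCOVA is r²·s1², which is also never negative. ANCOVA therefore matches or beats both, apart from the small cost of estimating the slope.

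**Equal standard deviations (assumed).** With s0 = s1 the three variances are proportional to 2(1 − r), 1 and 1 − r². ANCOVA relative to the change score is (1 − r²)/(2(1 − r)) = (1 + r)/2. ANCOVA relative to the 1-month score is 1 − r².

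| Assumed r | ANCOVA / change score | ANCOVA / 1-month score |
|---|---|---|
| 0.3 | 0.65 | 0.91 |
| 0.5 | 0.75 | 0.75 |
| 0.7 | 0.85 | 0.51 |

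Against the change score the variance is 35%, 25% and 15% lower. The standard error is 19%, 13% and 8% lower (square roots 0.806, 0.866 and 0.922).

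**Simulation.** In 4,000 simulated trials per value of r, with 278 per arm, the standard deviations of the estimate (change / 1-month / ANCOVA) were 0.100 / 0.083 / 0.079 at r = 0.3, 0.084 / 0.084 / 0.073 at r = 0.5, and 0.065 / 0.085 / 0.060 at r = 0.7. These agree with the formulas.

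**What it means for power.** For an assumed true difference of 0.2 SD, two-sided 5% and 278 per arm:

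| Assumed r | Change score | 1-month score | ANCOVA |
|---|---|---|---|
| 0.3 | 51% | 66% | 70% |
| 0.5 | 66% | 66% | 78% |
| 0.7 | 86% | 66% | 91% |

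**Where the gain disappears.** With equal standard deviations and r = 0.9, the ratio to the change score is (1 + 0.9)/2 = 0.95, a gain of only 5%. With r = 0.7 the gain is zero if s1/s0 = 1/0.7 = 1.43.

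**The case against.** The best defence is that nothing in section 5.12 is invalid. It is a generic paragraph in a journal article, does not mention quality of life by name, and allows linear regression if needed; endpoint-level covariates are often settled in an analysis plan. The first part stands: this is a question of efficiency. The second stands only in part. The article does choose tests and applies them to secondary outcomes, and the conditional regression sentence does not commit the trial to adjusting for the baseline score.

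The size of the gain is also fairly challenged. The correlation is assumed, and so is equality of the standard deviations, although the two measurements are taken in different clinical states: with the stone in place, and after treatment and scheduled stent removal. The power differences above belong to a small assumed effect. At 0.4 SD and r = 0.5, power is about 99.7% for the change score and above 99.9% for ANCOVA, so the choice would hardly matter.

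Three stronger readings are tempting, and the article supports none of them.

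- A reader might infer that the planned test is biased or distorted by chance baseline imbalance. Under 1:1 randomization such imbalance averages to zero, and its contribution is already in the t-test's standard error. What is lost is precision.
- A reader might turn the variance ratios into a shortage of patients. The trial is sized only for the stone-free rate and claims no power for quality of life.
- A reader might say that the Mann–Whitney route leaves no estimate in score points. Section 5.12 promises estimates with 95% confidence intervals, and a Hodges–Lehmann shift can accompany that test in score points.

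**Conclusion.** The point holds as a free improvement on one secondary endpoint. The stated comparison of Wisconsin score improvement is valid and unbiased, but it leaves available precision unused. Under an assumed correlation of 0.3 to 0.7 and equal standard deviations at both times, ANCOVA has 15–35% less variance than the change-score comparison. If the sponsor meant to compare 1-month scores only, the reduction is 9–49%. Neither assumption can be checked from the article, so these ranges are illustrative rather than a trial-specific loss. The direction does not depend on them: in large samples ANCOVA is not less precise than either alternative. The primary stone-free-rate analysis, the 8.5-point margin and the sample size are untouched.

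**What to change.** Add a sentence to section 5.12: the 1-month Wisconsin Stone QoL score will be analysed by linear regression on treatment, baseline score and centre (the stratification factor in section 5.5), and the adjusted mean difference will be reported with its 95% confidence interval. If residuals are skewed, use robust or bootstrap intervals rather than switching to Mann–Whitney, so that the estimated quantity stays the same whatever the distribution looks like. Regressing the change on the same terms gives an identical treatment coefficient, so the result can still be read as a difference in improvement.

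The cost is one sentence. No extra patients, visits or data are needed. With 556 evaluable patients the two-group test has 554 degrees of freedom; the baseline score uses one, and terms for 20 centres use 19 more, leaving 534. The sentence should be fixed before any unblinded results are seen, because adjustment added later could look selective.

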## BACKGROUND

1

Lower pole renal stones measuring 1–2 cm pose a unique endoscopic challenge, as there is currently no clear indication or contraindication favouring one treatment modality over the other. The latest European Association of Urology guidelines^1^ advise that, in the presence of unfavourable lower pole anatomy, “endourology” should be the first‐line approach. However, it is unclear whether flexible ureteroscopy (f‐URS) or percutaneous nephrolithotomy (PCNL) is preferred. Mini‐PCNL achieves high stone‐free rates (SFRs) but carries a greater risk of bleeding and tract‐related morbidity.^2^ In contrast, conventional f‐URS offers a minimally invasive alternative yet often results in lower SFRs in the dependent lower calyx due to difficult deflection angles, resulting in suboptimal access and fragment evacuation.^3^, ^4^

In recent years, f‐URS technology has made monumental advances. The advent of the flexible and navigable suction ureteral access sheath (FANS) and enhanced single‐use digital ureteroscope deflection mechanics allows navigation of the FANS and ureteroscope tip into target calyces that were previously challenging to reach, mitigating the traditional disadvantages of retrograde access.^5^ Current FANS and flexible ureteroscope technology have brought about active fragment evacuation, markedly enhanced intraoperative visibility, reducing intrarenal pressure and facilitating complete stone clearance in the current suction endourology era.^6^, ^7^

Given these technological improvements, several observational studies have reported favourable outcomes for FANS f‐URS in managing lower pole stones.^4^, ^8^ Currently, there is still a paucity of high‐level evidence to determine whether FANS f‐URS can achieve comparable efficacy to mini‐PCNL. With the aim of addressing this evidence gap and potentially expanding the armamentarium for intermediate‐sized renal calculi, we have designed an international, multicentre, randomized non‐inferiority trial comparing FANS f‐URS with mini‐PCNL in this challenging cohort. This study is titled the FLAME trial, an acronym for: Flexible ureteroscopy for Lower pole stones And Mini pErcutaneous nephrolithotomy.

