### Operation protocol

5.7

A standardized operating methodology, approved by the principal investigator at each centre, will be implemented to ensure consistency across sites. Monthly monitoring visits will be conducted to verify adherence to the protocol and address any procedural deviations.

All patients will undergo non‐contrast CT and intravenous pyelogram preoperatively to confirm stone location and measure stone diameter, area and volume, as well as to assess the infundibulopelvic (IP) angle and infundibular length and width.^12^ Stone burden and density will be quantified using the same validated software at each centre. Standard perioperative antibiotic prophylaxis—either cefuroxime 1500 mg or levofloxacin 500 mg—will be administered 30 minutes before the procedure. Patients with a positive preoperative urine culture will receive tailored antibiotic therapy for 5–7 days based on sensitivity results prior to surgery.

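### The primary stone-free comparison is unadjusted and regression is left to an undefined condition, although stone burden and lower-pole anatomy are assessed in every patient: a valid analysis, but an avoidable loss of precision and an open choice of model

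*Protocol article*

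**What the plan says.** Section 5.12 of the protocol article covers primary and secondary outcomes in one paragraph. For outcomes such as stone-free status it says: "Categorical data will be presented as frequency (rate) and analysed using the chi‐square test or Fisher's exact test". Estimates with 95% confidence intervals are then compared with the non-inferiority margin. Covariate adjustment appears in one conditional sentence: "If multivariate analysis is required, multiple linear regression or logistic regression models will be employed". Nothing states what would make such a model necessary, which variables would enter it, or on what scale its result would be reported. IP angle is named only as a subgroup factor, and stone burden is not named in the section.

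Section 5.7 requires preoperative imaging, by non-contrast CT and intravenous pyelogram, in all patients. The purposes include to "measure stone diameter, area and volume, as well as to assess the infundibulopelvic (IP) angle and infundibular length and width". Stone burden and density are quantified with the same validated software at every centre.

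Section 5.11 sets the design: "we therefore assume an immediate SFR of 85% for both" arms, a "margin of 8.5% has been selected" as an absolute reduction, and "the required sample size is 278 participants per group (totalling 556").

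**The concern.** The verdict depends on whether one confidence limit for a difference in proportions lies above -8.5 points, in a trial planned at 80% power. The outcome is residual stone on CT. Its natural baseline counterpart, the amount of stone at the start, is recorded for everyone. Adjusting for baseline variables that predict the outcome narrows the interval and removes the effect of chance imbalance in them, at no cost in patients or visits. The text fixes an analysis that uses none of this.

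Two features of the conditional sentence add to the concern. With no trigger or covariate list, the decision to adjust, and for what, can be made with outcome data in hand. And the usual output of the logistic model it offers is an odds ratio, which cannot be set against an absolute margin unless it is converted to a risk difference. The article does not mention a conversion.

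**Working it through.** **Inputs from section 5.11.** SFR 85% in both arms, margin 8.5 points, alpha 2.5%, power 80%, 278 per arm before losses, 320 per arm enrolled, 15% anticipated loss. Evaluable per arm after that loss: 320 x 0.85 = 272.

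**Reproducing the plan's figure.** With an unadjusted variance and one-sided 2.5%:

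n = 2 x 0.85 x 0.15 x (1.960 + 0.842)^2 / 0.085^2 = 277.02, rounded up to 278.

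This equals the stated figure, so the sample size was built for an unadjusted comparison.

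**Unadjusted power.** Power = Phi(0.085 / SE - 1.960), with SE = sqrt(2 x 0.85 x 0.15 / n).

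- n = 278: SE = 0.0303, 0.085 / SE = 2.807, power 80.1%.
- n = 272: SE = 0.0306, 0.085 / SE = 2.776, power 79.3%.
- n = 320 (no loss): power 85.3%.

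**Adjusted power.** Let R2 be the share of outcome variance explained by the baseline covariates. The article gives no value, so 0.02 to 0.15 is an assumed range.

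- Prognostic equally in both arms: the variance is multiplied by (1 - R2).
- Prognostic in one arm only: write s^2 for the outcome variance. The variance of the adjusted difference is s^2(1 - R2)/n + s^2/n + R2 s^2/(2n) = (2s^2/n)(1 - R2/4). The saving is a quarter as large.

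Power at 272 per arm:

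| Assumed R2 | Both arms | One arm only |
|---|---|---|
| 0 (unadjusted) | 79.3% | 79.3% |
| 0.02 | 80.1% | 79.5% |
| 0.05 | 81.3% | 79.8% |
| 0.10 | 83.3% | 80.3% |
| 0.15 | 85.3% | 80.8% |

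The 95% interval half-width at 272 per arm is 6.0 points unadjusted, 5.7 at R2 0.10 and 5.5 at R2 0.15 (both arms).

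**Check by simulation.** 6,000 trials per setting, 272 per arm, one baseline score prognostic in both arms. A logistic model with treatment and score, standardised to a risk difference, was set against the unadjusted difference.

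| Odds ratio per SD | R2 (about) | Unadjusted | Adjusted |
|---|---|---|---|
| 1.5 | 0.02 | 79.2% | 79.9% |
| 2.0 | 0.06 | 79.5% | 81.4% |
| 2.5 | 0.10 | 79.1% | 83.1% |
| 3.0 | 0.14 | 79.3% | 85.1% |

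The simulation agrees with the formula. At a true difference of -8.5 points, both methods declared non-inferiority in 2.6% to 2.9% of trials, so adjustment did not add to the false-positive rate.

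**The case against.** **The unadjusted test is valid and the design agrees with it.** This stands. The 278 reproduces from the unadjusted formula, so nothing is miscalculated or contradictory.

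**Covariate lists and functional forms belong in a statistical analysis plan that is not shown.** This stands in part. The absence of a covariate list alone would be no finding, and it would be too strong to say that stone burden can enter no analysis. But the article itself states an unadjusted test and makes adjustment conditional, and that is the text at issue.

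**The Background does not show that anatomy predicts SFR in both arms.** This stands. A reader might infer that the protocol declares lower-calyx anatomy prognostic throughout. The phrase "lower SFRs in the dependent lower calyx due to difficult deflection angles, resulting in suboptimal access and fragment evacuation" describes conventional flexible ureteroscopy only. The next paragraph says the suction sheath reduces that disadvantage, and neither paragraph says that anatomy lowers SFR with mini-PCNL. The one-arm column is therefore a realistic case for IP angle.

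**The population is narrow.** Eligibility is limited to 1-2 cm lower pole stones, which restricts the spread in stone size and hence R2. This limits the gain but does not remove it: for stones of similar shape, a twofold range in diameter is about an eightfold range in volume (2^3 = 8), multiple stones are eligible, and no criterion restricts density or IP angle.

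**The analyst is blinded until interpretation is complete.** This reduces the risk of a convenient model choice. It does not remove it, because results under coded groups still show whether adjustment changes the conclusion.

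**A logistic model can yield a risk difference.** True, and the fix relies on it. The article does not say that it will be done.

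**Conclusion.** The point holds as lost efficiency together with an unspecified modelling choice. It is not an error in the primary analysis or the sample size.

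The size rests wholly on an assumed R2. For R2 of 0.02 to 0.15 in both arms, power at 272 evaluable per arm rises from 79.3% to between 80.1% and 85.3%, a gain of about 1 to 6 points. If the covariates matter in one arm only, the gain over the same range is 0.2 to 1.5 points, or about 1 point. Gains near 10 points would need R2 of about 0.25 (89.4% at 272 per arm in both arms), and nothing in the article supports so high a value.

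A reader might also infer that the trial is underpowered or its conclusion unsafe for want of adjustment. The article does not support that: the unadjusted analysis has close to its nominal power under the plan's own assumptions. The case for the change is that it is nearly free, loses almost nothing if the covariates prove weak, and settles the model before outcomes are seen.

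**What to change.** For the primary endpoint, replace the conditional regression sentence in section 5.12 with wording such as:

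*The primary analysis estimates the difference in immediate SFR (FANS f-URS minus mini-PCNL) by marginal standardisation from a logistic model with treatment, baseline stone volume (log scale) and IP angle (continuous), with a robust 95% confidence interval. Non-inferiority is concluded if the lower limit is above -8.5 percentage points. The unadjusted risk difference with its 95% confidence interval is reported as a sensitivity analysis.*

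The choice of these two covariates is a judgement. Density or infundibular dimensions could be named as well, provided the list is fixed before outcome data are examined. How centre is handled is a separate matter.

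The cost is wording in the protocol or analysis plan, with no new data, visits or patients. There are two small downsides: standardisation may need a routine outside SPSS 20, and any missing baseline values need a simple prespecified imputation so that all randomised patients stay in the analysis.
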